### 2.8. Participant Timeline

Table 2 provides an overview of the time schedule of enrolment, interventions, main study visits and assessment measures for participants. Each of the visits is explained in detail below.

Visit −3 (day −60/−45): Invitation to participate. Potential eligible primary healthcare professionals will receive the invitation by email. Once they agree to participate and sign the informed consent form, will be randomized. Potentially eligible participants will receive the invitation by SMS.

Visit −2 (day −45/−7): Participants’ recruitment and baseline interview. The research assistant will contact potential participants via phone. On this call, patients will be given thorough information on the study and, if willing to participate, they will be asked for informed consent. On the same call, a basal interview (behavioural and psychological outcomes) will be performed.

Visit −1 (day −7/−1): Baseline data collection. Participants who signed the informed consent will undergo baseline data collection at the hospital (anthropometric measurements, blood pressure and blood laboratory examinations).

Visit 0 (day 0): Initiation of the intervention. Patients in the Intervention A and Intervention B group will receive their first SMS. Patients in the control group will be informed of their allocation. Health professionals who have been assigned to the intervention B group will take the online education. They will have 4 weeks to complete it.

Visit 1 (month 6): Post intervention data collection. After 6 months of intervention, data collection from patients will be performed following the same procedure as at baseline time basal interview. Interview on behavioural and psychological outcomes will be conducted by phone, and anthropometric measurements, blood pressure and blood laboratory examinations at the Clinical trial Platform at IdISBa. Data collection from health professionals will also be accomplished during this time, through individual interviews (only with Intervention B group professionals) and by delivering an online questionnaire.

### 2.9. Data Collection

We will collect specific data from participating patients and healthcare professionals.

At the patient level, baseline data will be collected over the phone immediately after recruitment with a structured interview using the Lime Survey online tool. Patients will subsequently be invited to attend a visit at the IdISBa Clinical Trial Platform, for the collection of basal clinical and physiological data by a research nurse. Post-intervention data will be collected after 6 months in the same way as in baseline data collection. We will also examine the proportion of participants exposed to the intervention (i.e., successfully receiving messages) at 6-months follow-up and conduct around 15 individual interviews to explore patient experiences with the intervention.

At the professional level, data collection will be conducted using structured questionnaires to (1) examine the proportion of primary healthcare professionals actively adopting the intervention program and (2) assess the extent to which they improved their clinical management of prediabetes. We will also conduct around 10 individual interviews with primary healthcare professionals with high or low implementation ratios to identify barriers to intervention delivery and implementation.

### 2.10. Outcome Measures

The primary outcome measure will be glycated haemoglobin (HbA1c) at 6 months follow-up. Secondary outcome measures will include:

(A) Clinical and physiological outcomes: Fasting blood glucose, triglycerides, total cholesterol, low density lipoprotein cholesterol (LDL), high density lipoprotein cholesterol (HDL), lipoprotein A, aspartate aminotransferase enzyme (AST), alanine aminotransferase (ALT), gamma glutamyl transpeptidase (GGT), complete hemogram, creatinine, serum albumin, insulin, urinary sediment, albumin-creatinine ratio, body weight, waist circumference, blood pressure, and cardiovascular disease risk [44].

(B) Diabetes incidence: proportion of patients with a new diagnosis of T2DM.

(C) Motivational and behavioural outcomes: brief motivation questionnaire (ad hoc); adherence to the Mediterranean diet, measured with MEDAS questionnaire [45]; physical activity, measured with REGICOR Short form Physical Activity Questionnaire [46]; sedentary behaviour, measured with the Spanish version of the physical activity questionnaire used in the Physical activity questionnaire from the Nurses’ Health Study [47]; smoking habit, measured with an adapted version of the Global Adult Tobacco Survey: GATS questionnaire; and alcohol consumption will be collected.

(D) Trial feasibility outcomes: numbers of eligible patients, recruitment rate, follow-up rate.

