#### 2.4.2. Patients

Selection criteria: We will include patients between 18–75 years old, registered in the Public Health Service of the Balearic Islands, at risk of T2DM (HbA1c from 6% to 6.4% in the last three months, two consecutive values of fasting plasma glucose between 110–125 mg/dL, or both) [23], with access to a mobile device able to receive text messages. We will exclude those not able to read messages in Spanish or with severe mental conditions. Patients taking antidiabetic drugs will also be excluded as well as women who gave birth in the previous 12 months or that are currently pregnant and people planning to change healthcare centre during the intervention period.

Recruitment procedure: With support from the PRISIB platform (health information platform of the Health Research Institute of the Balearic Islands), we will extract from electronic health records a list of all patients from the health professionals previously recruited with a record during the last 12 months of: (1) HbA1c from 6–6.4% or (2) two consecutive values of fasting plasma glucose between 110–125 mg/dL or (3) both. Starting from those patients with most recent blood test determinations available, we will send to patients an SMS inviting them to participate in the study. This SMS will include a link to a website containing information about the study (brief summary, patient information sheet, and informed consent). Within the next 48 h, a research assistant will phone them to formally invite them to participate in the study, provide additional information (if needed), and obtain the informed consent (audio-recorded over the phone). Blood tests will be ordered for all patients with test results recorded more than three months ago from the recruitment date to confirm patient eligibility.

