### 2.7. Interventions

#### Description of the Intervention Group (SMSs)

In the Intervention A group, patients will receive the text messaging intervention, with a frequency of 3 to 5 messages per week, depending on the results of the pre-pilot stage (project stage 4), where the perception of the participants will be assessed, both in terms of frequency and content of the SMS. Messages will be received from Monday to Friday, never on weekends or holidays because of technological limitations of the system available to be used. The structure of the messages will be designed to vary the subject matter (motivation, type of food, portions, physical activity, sedentary lifestyle, etc.); as well as to follow a progression in the complexity of the messages and the physical activity recommendations.

The messages will focus on nutrition and physical activity. In terms of nutrition, recommendations will be given on the type of carbohydrates that are most suitable to prevent glycaemic peaks, portions, and frequency of consumption of food groups, ultra-processed foods and others for occasional consumption, alcohol consumption and energy drinks, as well as recipe examples [39,40,41]. In terms of physical activity, messages will include recommendations to increase the frequency, intensity and duration of physical activity, strategies to reduce sedentary behaviour, and strategies to replace sedentary time with physical activity time [42,43]. In addition, we will include motivational messages, as well as other personalized messages for participants who need to lose weight or who are smokers.

In the intervention B group, patients will receive the same text messaging intervention as in group A, and in addition, their primary healthcare professionals will receive online education on the management of patients with prediabetes at the primary healthcare level. The online education for healthcare professionals will consist of written material on how to achieve behavioural changes and what recommendations are appropriate for a population with prediabetes in terms of diet, exercise and diabetes prevention. They will also be provided with video examples of clinical consultations. These interviews have been designed by a group of experts, including sports scientists, dietitian-nutritionists, GPs, psychologists, and nurses.

Control group participants will receive usual care, and their healthcare professionals will not receive online education.

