### 2.11. Data Analysis

We will use descriptive statistics to explore the characteristics of the participants at baseline. To estimate the presence and magnitude of a potential selection bias, we will compare the characteristics of healthcare professionals and patients recruited vs the characteristics of the complete population of healthcare professionals and patients meeting our eligibility criteria (defined above). The impact of the intervention will be measured in terms of the difference between groups in the primary and secondary outcomes after the 6-month intervention period. For that end, we will build general linear models (ANCOVA), adjusting for baseline values. All the analyses will be conducted by the intention to treat (ITT) approach. Missing values will be replaced using the multiple imputation model (MICE) [48].

Statistical analysis will be performed using SPSS v.25 (IBM, New York, NY, USA) and Stata v.16 (Statacorp, College Station, TX, USA), and we will use an α of 5% throughout.

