**Figure 4 ijerph-19-14706-f004:**
[figure not shown]
Phase II PreDiabeText study timeline.

**Table 1 ijerph-19-14706-t001:** Brief structured summary of the trial.

Data Category	Information
Trial identification number	ClinicalTrials.gov NCT05110625
Date of registration	8 November 2021
Sponsor	Balearic Islands Research Institute (IdISBa), Spain
Contact for public and scientific queries	[name] [name]. Primary Care Research Unit of Mallorca (IB-Salut), Balearic Health Service, Palma de Mallorca, Spain, Palma de Mallorca, [contact]
Scientific title	Effects of a low intensity, multifaceted, mHealth intervention to prevent type 2 diabetes mellitus in adults with prediabetes in the primary care setting (the PREDIABETEXT trial)
Country of recruitment	Spain
Health condition studies	Prediabetes
Interventions	Intervention A: Participants will receive text messages (three per week) in their mobile phones during six months Intervention B: Participants will receive messaging intervention plus online education to their primary healthcare workers
	Control: Participants will receive usual care only, and their healthcare workers will not receive online education
Inclusion/exclusion criteria	Eligible age: 15–75 years; eligible sex: males and females.
	Inclusion criteria: Registered in the Public Health Service of the Balearic Islands. HbA1c from 6% to 6.4% or fasting plasma glucose 110–125 mg/dL, or both. With access to a mobile device able to receive text messages.
	Exclusion criteria: documented history of T2D and/or use of oral antidiabetic medication. Younger than 18 years old or older than 75 years old. People not able to read messages in Spanish. Patients with severe mental conditions.
Study type	Interventional
	Allocation: randomized; Intervention model: parallel assignment; masking: none (open label)
	Primary purpose: Change from Baseline HbA1C at 6 months
Date of first enrolment	1 September 2021
Target sample size	420 (140 participants in each group)
Recruitment status	Actively recruiting
Primary outcomes	Reduction of HbA1C
Secondary outcomes	Fasting blood glucose, body weight, waist circumference, blood pressure, lipids, cardiovascular disease risk, proportion of patients developing T2DM, adherence to Mediterranean diet, physical activity, sedentary behaviour, smoking habit, alcohol consumption

**Table 2 ijerph-19-14706-t002:** Participants main visits and assessment schedules.

Main Visits and Assessment Schedules					
Visit	V −3	V −2	V −1	V 0	V 1

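### Diabetes incidence is assigned a linear ANCOVA that does not fit it, and its definition leaves open the source and threshold of diagnosis and the handling of baseline values already in the diabetic range

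*Protocol article*

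**What the plan says.** **Outcome.** Section 2.10, item (B), gives "Diabetes incidence: proportion of patients with a new diagnosis of T2DM". Table 1 words it as "proportion of patients developing T2DM". Neither place gives a biochemical threshold or says whether the diagnosis comes from the trial's own blood tests or from the clinical record.

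**Analysis.** Section 2.11 measures impact as the "difference between groups in the primary and secondary outcomes after the 6-month intervention period". It then names general linear models (ANCOVA) with adjustment for baseline as the means of doing so. No exception is made for binary outcomes and no cluster term is mentioned.

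**Entry.** Section 2.4.2 admits patients with "HbA1c from 6% to 6.4% in the last three months, two consecutive values of fasting plasma glucose between 110–125 mg/dL, or both". The marker on which the patient did not qualify has no upper limit. On re-testing, the section says: "Blood tests will be ordered for all patients with test results recorded more than three months ago from the recruitment date to confirm patient eligibility". More recent results need no confirmation.

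**Known diabetes.** Table 1 lists "Exclusion criteria: documented history of T2D and/or use of oral antidiabetic medication". Section 2.4.2 excludes users of antidiabetic drugs but does not mention documented diabetes.

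**Timing.** Table 2 puts the eligibility check at Visit −2 and the baseline bloods, including glucose and HbA1c, at Visit −1. The same bloods are taken in all arms at Visit 1 (month 6).

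**Intervention B.** In this group, says Section 2.7, "their primary healthcare professionals will receive online education on the management of patients with prediabetes at the primary healthcare level". Professionals in the other two groups receive no such training.

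**The concern.** There are two separate problems.

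The first is the model. Diabetes incidence is a yes/no outcome in people who are all meant to be free of diabetes at the start. Adjusting for its own baseline value adjusts for a constant. What remains ignores the randomisation of professionals rather than patients and makes no use of baseline HbA1c, the obvious prognostic covariate.

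The second is the definition. Someone who enters on fasting glucose may have an HbA1c above 6.4% at Visit −1, or the reverse, and no rule says whether that person can later count as a new case. If the source of diagnosis is usual care, the group whose professionals are trained in prediabetes may also find more cases.

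With few events expected, a handful of misclassified patients per arm matters. Cases already present at baseline would pull a real difference towards nothing, and uneven detection could make the intervention B group look worse than it is.

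**Working it through.** The protocol gives no figure for incidence. The only stated figure used here is the design effect, which reproduces.

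**Inputs from the protocol:** 140 patients per arm, 10 per professional, intraclass correlation 0.04, dropout 10% (Section 2.5); annual conversion 5–10% (Introduction); α 5% (Section 2.11).

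**1. Design effect.** 1 + (10 − 1) × 0.04 = 1.36, as stated.

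**2. What the ANCOVA becomes.** The model has an intercept, two arm indicators and baseline status. Baseline status is 0 for everyone, so the four-column design matrix has rank 3. The covariate drops out and a linear comparison of proportions remains.

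**3. Error rate of that comparison.** With independent patients, 20,000 simulated trials of 140 per arm gave a type I error of 4.7% at a 2.5% risk and 5.2% at a 5% risk. Linearity alone does little harm here. If clustering is present but ignored, the effective critical value is 1.96/√(design effect):
- Correlation 0.04 (the protocol's value for HbA1c, assumed to apply): 1.96/√1.36 = 1.68, a true two-sided level of about 9%.
- Half that, 0.02 (assumed): design effect 1 + 9 × 0.02 = 1.18; 1.96/√1.18 = 1.80, about 7%.
- Zero: 5%.

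**4. Expected true events.** Completers per arm: 140 × 0.9 = 126. Six-month risk = 1 − (1 − annual rate)^0.5.
- 5% a year: 1 − 0.95^0.5 = 2.53%; × 126 = 3.2 events.
- 10% a year: 1 − 0.90^0.5 = 5.13%; × 126 = 6.5 events.

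**5. Cases already present at baseline.** Let q be the share of an arm in the diabetic range at Visit −1, all of them later counted as new. The protocol does not give q; 2–5% is an assumed range. True events = 126 × (1 − q) × risk; cases already present = 126 × q. If the latter do not respond to the intervention, a true 40% relative reduction shows as 40% × (1 − their share of all counted cases).

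| q | Annual rate | True events | Already present | Share of counted cases | 40% reduction shows as |
|---|---|---|---|---|---|
| 2% | 5% | 3.1 | 2.5 | 45% | 22% |
| 2% | 10% | 6.3 | 2.5 | 28% | 29% |
| 5% | 5% | 3.0 | 6.3 | 68% | 13% |
| 5% | 10% | 6.1 | 6.3 | 51% | 20% |

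**6. Detection.** If diagnosis came from usual care, and 50% of cases were found in control against 60% or 80% in the intervention B group (all assumed), the false risk ratio would be 0.60/0.50 = 1.2 or 0.80/0.50 = 1.6. With the trial's own bloods as the source it would be 1.0.

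**The case against.** **The ANCOVA sentence may be shorthand.** Section 2.10 also lists feasibility measures such as the recruitment rate among the secondary outcomes, and no baseline-adjusted ANCOVA can be fitted to those. The sentence may therefore be meant only for continuous outcomes, with the rest left to an unseen analysis plan. That is plausible. But the article names one method for all outcomes and no other, so the stated method is the one to assess. It is also fair that the reduced model still estimates a difference in proportions, which is the measure recommended below. A reader might infer that normal-theory inference breaks down at these counts; the simulation with independent patients does not support that. The faults are the ignored clusters and the empty adjustment.

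**The protocol does not say that existing cases are counted.** A reader might infer that it does. The outcome is worded as a new diagnosis, Table 1 excludes documented diabetes, and a person with a documented diagnosis would not naturally be a new case. What stands is narrower: undiagnosed patients in the diabetic range on one marker are not ruled out, and their Visit −1 values will be on file with no rule for them.

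**The protocol does not say that the patient's own professional makes the diagnosis.** Bloods are taken in every arm at month 6, and Section 2.6 blinds outcome assessors, so a laboratory reading is equally open. The described training does not mention screening or diagnostic testing. What stands is that the source is unstated, and that blinding assessors does not blind treating professionals if the clinical record is used.

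**Importance.** The Limitations section says the trial is not powered for prevention of T2DM. Sections 2.5 and Limitations tie the phase III step to HbA1c and feasibility, so the documents do not support a claim that this outcome decides that step. This limits the weight of the point but does not remove it.

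**Conclusion.** The point holds in a limited form. As written, Section 2.11 gives diabetes incidence a linear ANCOVA whose baseline term is constant and which has no cluster term. The cost is a test that would run at about 9% instead of 5% if the design effect planned for HbA1c carried over, and less if the correlation for this outcome is smaller.

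The definition leaves room for existing cases and for uneven detection; neither is stated to occur. With about 3 to 6 true events per arm, an assumed 2–5% of patients already in range and counted would make up about 28–68% of cases and shrink a true 40% reduction to about 13–29%. These figures assume that all such patients are counted and are equally common in each arm. Balanced cases of this kind dilute a difference; a reader might infer that they reverse it, but in expectation they do not.

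The outcome is secondary and unpowered. It should still be fixed, because the correction is cheap and uses data already scheduled.

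**What to change.** 1. Define incident T2DM by one laboratory rule, the same in all arms, from the Visit 1 HbA1c and fasting glucose. Report clinician-recorded diagnoses separately.
2. For this outcome only, take as the at-risk denominator the patients whose Visit −1 values do not exceed the trial's own upper limits (HbA1c 6.4%, fasting glucose 125 mg/dL). These values precede the first message and the training. Give the count among all randomised patients as a sensitivity analysis, in keeping with the intention-to-treat statement in Section 2.11.
3. Reconcile Section 2.4.2 with Table 1 on documented diabetes.
4. In Section 2.11, replace linear ANCOVA for this outcome with a cluster-aware binary analysis suited to few events, such as a cluster permutation test, or GEE or mixed logistic regression with a small-sample correction. Adjust for baseline HbA1c and report a risk difference with a confidence interval.

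The cost is a change of wording and slightly more analysis work. A few patients leave the denominator of this one outcome. No new measurements are needed, and the primary analysis is untouched.

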### 2.11. Data Analysis

We will use descriptive statistics to explore the characteristics of the participants at baseline. To estimate the presence and magnitude of a potential selection bias, we will compare the characteristics of healthcare professionals and patients recruited vs the characteristics of the complete population of healthcare professionals and patients meeting our eligibility criteria (defined above). The impact of the intervention will be measured in terms of the difference between groups in the primary and secondary outcomes after the 6-month intervention period. For that end, we will build general linear models (ANCOVA), adjusting for baseline values. All the analyses will be conducted by the intention to treat (ITT) approach. Missing values will be replaced using the multiple imputation model (MICE) [48].

Statistical analysis will be performed using SPSS v.25 (IBM, New York, NY, USA) and Stata v.16 (Statacorp, College Station, TX, USA), and we will use an α of 5% throughout.

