#### 2.3.5. STAGE 5: Phase II Trial to Explore Interventions Efficacy and Identify Implementation Barriers

Stage 5 of the study will consist of a Phase II, six-month, three-arm, cluster randomized, clinical trial (Figure 3 and Figure 4). The protocol of this phase II trial was registered on clinicaltrials.gov (NCT05110625) (**Protocol version: v1.1, 16/08/2022**). Table 1 summarizes all items included in the trial registry, as suggested by the World Health Organization [36].

In the Intervention A group, patients will receive the text messaging intervention. In the intervention B group, patients will receive the text messaging intervention and their primary healthcare professionals will receive the online education intervention. Control group participants will receive usual care, and their healthcare professionals will not receive the online educational intervention.

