### 2.5. Sample Size Determination

The sample size was estimated based on HbA1c as the main outcome variable. We plan to recruit 42 primary healthcare nurses or GPs and 420 patients (10 patients per provider). Assuming an 80% power, an intraclass correlation coefficient of 0.04 [37], a design effect of 1.36, and a dropout rate of 10%, our sample-size calculation indicates that 420 patients (control group: 140; Intervention group A: 140; Intervention group B: 140) would allow us to detect a difference in HbA1c of at least 0.3% between the control and the intervention groups (assuming standard deviation = 0.8%). According to previous research [38], this difference would allow us to detect statistically significant differences in diabetes incidence in a future phase III trial with a longer (at least 12 months) follow-up.

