### 2.6. Randomization and Masking

Family physicians or nurse participants in the study will be randomized by computer-generated random numbers to one of the three arms of the study. Patients from each physician’s or nurse’s will be invited to participate and will receive the intervention according to their physician or nurse arm allocation: Arm 1: healthcare professionals will receive online training and their patients will receive SMS; Arm 2: their patients will receive SMS; Arm 3 (control group): usual care. Outcome assessors will be blinded to treatment allocation.

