**Participants—health care workers**					
Invitation by email	X				
Informed consent	X				
Inclusion/exclusion criteria	X				
Randomization	X				
Online education (intervention B group)				X	
Individual interviews (intervention B group)					X
Interview: Knowledge and attitudes about prediabetes, and communication skills					X
Trial feasibility: follow-up rate					X

1. Time point: d = day; m = month; 2. SB assessment: NHS questionnaire; 3. Dietary assessment: MedDiet adherence questionnaire; 4. Motivation Questionnaire (ad hoc); 5. PA assessment: REGICOR PA questionnaire; 6. Randomization: Patients and healthcare workers will be randomised at the same time, with only the healthcare worker being randomised, and their 10 patients being assigned to the same intervention group as the healthcare workers; 7. Blood laboratory examinations: glucose, HbA1C, total cholesterol, HDL-c, LDL-c, TG, Hb, MCV, serum creatinine, AST, ALT, and GGT. TyG index and FLI will be calculated; 8. Anthropometric measurements: body weight, WC and HC, BMI, body composition, height; 9. Blood pressure measurement: the arm with the highest blood pressure. Subsequent blood pressure measurements will be taken in this arm throughout the study; 10. Initiation of intervention: initiation of SMS sending.

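### The stated primary analysis is a plain ANCOVA with no term for the randomised professional: at the plan's own ICC a nominal two-sided 5% test runs at about 9%, with confidence intervals 13–14% too narrow.

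*Protocol article*

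**What the plan says.** Section 2.3.5 of the protocol article describes a "Phase II, six-month, three-arm, cluster randomized, clinical trial". Section 2.6 makes the professional the unit of allocation: "Family physicians or nurse participants in the study will be randomized by computer-generated random numbers to one of the three arms of the study". Patients take the arm of their professional. Footnote 6 to Table 2 says the same, "with only the healthcare worker being randomised, and their 10 patients being assigned to the same intervention group as the healthcare workers".

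Section 2.5 plans 42 professionals and 420 patients, 10 per professional and 140 per arm. It allows for clustering: "Assuming an 80% power, an intraclass correlation coefficient of 0.04 [37], a design effect of 1.36, and a dropout rate of 10" per cent.

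Section 2.11 gives one model for the between-group comparison of primary and secondary outcomes at 6 months: "For that end, we will build general linear models (ANCOVA), adjusting for baseline values". Alpha is 5% throughout, and the section does not say whether tests are one- or two-sided. Missing values are to be handled by MICE. Neither section 2.11 nor any other part of the article mentions a random effect, GEE, cluster-robust standard errors or a cluster-level summary.

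**The concern.** A general linear model assumes independent errors. Section 2.5 assumes that they are not independent: patients of one professional share a correlation of 0.04, and the sample size is raised by 36% for that reason. An analysis that drops the correlation treats each arm as 140 independent patients (126 if 10% are lost), when it really rests on 14 randomised professionals. The treatment estimate is not biased by this, but its standard error is too small, so p-values are too low and confidence intervals too narrow.

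The consequence is practical. Section 2.2 states a hypothesis that the interventions lower HbA1c by at least 0.3% against control, and the Limitations make a phase III trial depend on favourable results here. A test with too high an error rate would feed that decision. Intervention B also acts through the professional, so variation between professionals bears directly on that comparison.

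**Working it through.** **Inputs.** From section 2.5: 42 professionals, 10 patients each, 14 professionals per arm, ICC 0.04, design effect 1.36, dropout 10%, difference 0.3, SD 0.8, power 80%. From section 2.11: alpha 5%. Assumptions made here: a two-sided test for the main check, and an ICC of 0.04 that also applies to the residuals after baseline adjustment.

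**1. The plan's own figures.**
- Design effect = 1 + (m − 1) × ICC = 1 + 9 × 0.04 = 1.36, exactly as stated.
- One-sided 5%: 88 per arm × 1.36 ≈ 120; 120 / 0.9 ≈ 133; rounded up to 14 whole clusters of 10 this is 140 per arm, 420 in total. This matches.
- Two-sided 5%: 112 × 1.36 ≈ 153; 153 / 0.9 = 170 per arm, 17 clusters, 510 in total. This does not match.

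The choice of sidedness behind the 420 is a separate matter. It is shown because it affects how the error rate below is read.

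**2. Understated standard error.** Ignoring clustering shrinks the standard error by the factor 1/√DE.
- 10 per professional: 1 − 1/√1.36 = 1 − 0.857 = 14%.
- 9 per professional after dropout: DE = 1 + 8 × 0.04 = 1.32; 1 − 1/√1.32 = 1 − 0.870 = 13%.

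**3. Real error rate of one comparison with control.** Two-sided: 2 × [1 − Φ(1.96/√DE)].

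| ICC | 9 per professional | 10 per professional |
|---|---|---|
| 0.01 | 5.9% | 6.0% |
| 0.02 | 6.9% | 7.1% |
| 0.04 (plan) | 8.8% | 9.3% |
| 0.05 | 9.8% | 10.4% |
| 0.10 | 14.4% | 15.5% |

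At the plan's ICC, nominal 95% intervals cover 100 − 8.8 = 91.2% or 100 − 9.3 = 90.7% of the time. If the 5% is one-sided, the rate at DE 1.36 is 1 − Φ(1.645/√1.36), about 8%.

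**4. Three-arm test.** For a 2-df test of any difference between arms, the rate is exp[−5.991/(2 × DE)]: 11.0% at DE 1.36 and 10.3% at DE 1.32.

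**5. Simulation of the named model.** 10,000 null trials were run with 42 clusters, residual ICC 0.04 and an assumed baseline–outcome correlation of 0.5. Each was analysed twice.

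| Analysis | 10 per professional | 9 per professional |
|---|---|---|
| Patient-level ANCOVA, no cluster term | 9.4% | 8.7% |
| Baseline-adjusted analysis of 42 cluster means (42 − 4 = 38 df) | 4.9% | 4.9% |

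The simulation agrees with the formula, and an analysis at the level of the professional restores the nominal rate.

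**The case against.** The strongest reply is that one sentence in a condensed article names a model family, not a method for standard errors, and that a fuller plan may specify clustering. A baseline-adjusted linear model with cluster-robust errors, or one fitted to cluster means, could loosely be called an ANCOVA. That is possible. But the article does more than stay silent: it names a model whose ordinary meaning is independent errors, in a trial whose sample size assumes the opposite. Someone who follows section 2.11 as written would run the wrong test.

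Several narrower objections stand in part:

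- **The 9% is conditional.** It needs an ICC of 0.04 in the baseline-adjusted residuals and a two-sided test. With an ICC of 0.01 to 0.02 it is not true that the error rate nearly doubles. Any positive ICC still inflates it, and 0.04 is the plan's own value.
- **The trial is phase II and partly exploratory.** The article also does not define the result that would trigger phase III, so no p-value threshold is shown to be the gate. Intervals with about 91% coverage would still mislead whoever weighs that decision.
- **Imputation.** The article says only MICE. Whether the imputation model carries the cluster is commonly left to a fuller plan, so this is not counted as an error.
- **Two comparisons against control.** The chance of a false positive across both is a multiplicity question and is left out of the size given here.

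**Conclusion.** The concern holds. Section 2.11 contradicts sections 2.3.5, 2.5 and 2.6 and footnote 6 to Table 2: the design and sample size are clustered and the stated analysis is not. Under the two assumptions listed in the working, the error rate of a nominal 5% comparison is about 9%, and the precision of every between-arm HbA1c estimate is overstated by 13–14%. The same fault reaches every secondary outcome with correlation within professionals, by an amount that depends on its own ICC. Because it affects the primary inference and can be corrected before any analysis, it must be fixed.

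**What to change.** Replace the model sentence in section 2.11 with an analysis that accounts for the randomised professional. A suitable wording: 6-month HbA1c will be analysed with a linear mixed model fitted by REML, with fixed effects for arm and baseline HbA1c, a random intercept for the randomised professional, and Kenward–Roger or Satterthwaite degrees of freedom because there are only 42 clusters. A baseline-adjusted analysis of professional-level means would also serve. Secondary outcomes should use the cluster-aware equivalent for their type. The same paragraph should state whether the 5% is one- or two-sided, and should say that the imputation model includes the professional as a level, so that it matches the analysis.

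The cost is one paragraph and somewhat more work on the imputation. Stata v.16, already named, fits the mixed model. No data collection or conduct changes. At the plan's design effect, standard errors and intervals widen by √1.36 = 1.17 compared with the plain ANCOVA, which is the allowance that section 2.5 already builds into the sample size.
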